**Methods and analysis:**

A prospective registration study will be opened in hospitals in which the involved multidisciplinary team members (radiologists, radiation oncologists, surgeons and pathologists) have received dedicated training to enhance knowledge and awareness of LLNs and in which standardised treatment including LLND has been implemented. Patients with rectal cancer and at least one enlarged LLN (short-axis ≥7.0 mm), or intermediate LLN (short-axis 5.0–6.9 mm) with at least one malignant feature on primary MRI, evaluated by a trained radiologist, are eligible. Patients will undergo neoadjuvant treatment by trained radiation oncologists, followed by TME surgery in combination with a minimally invasive, nerve-sparing LLND performed by trained surgeons. LLND specimens are evaluated by trained pathologists or grossing assistants. The primary outcome is LLR rate 3 years postoperatively. Secondary outcomes are morbidity, disease-free survival, overall survival and quality of life. To demonstrate a significant reduction in LLR rate from 13% (based on historical control data) to 6% after optimised treatment, 200 patients with enlarged LLNs are required.

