With recent publications, awareness concerning the importance of LLNs has gradually increased in the West. The international multicentre study by the Lateral Node Consortium found an increased LLR rate of up to 20% after 5 years for primarily enlarged LLNs (≥7.0 mm), which could be significantly lowered to a 3-year LLR rate of 6% with selective LLND after (C)RT.^6^ A second study, the Snapshot Rectal Cancer 2016 study, included 3057 patients operated on for rectal cancer in 2016 in 67 Dutch centres and demonstrated a 3-year LLR rate of 11% (4 years 15%) for patients with enlarged LLNs after (C)RT+TME.^14^ While some other studies remained inconclusive about the influence of malignant features,^5 15^ that study demonstrated additional prognostic value for the presence of malignant features (round shape, irregular margins, loss of fatty hilum and heterogeneity) in intermediate size LLN (short-axis 5.0–6.9 mm), as presence increases the LLR risk from 2% to 8%.^14 16^ Moreover, in both the Consortium and the Snapshot study, LLN enlargement was not associated with increased distant metastases rates, indicating that enlarged LLNs should be considered a locoregional disease, requiring additional treatment.^11 17^

To further increase awareness and knowledge about lateral nodal disease, the Dutch radiologists, radiation oncologists and surgeons participated in training sessions.^18 19^ Radiologists followed a training session provided by expert radiologists, resulting in better short-axis measurements and anatomical classification of LLNs in cases assessed after the training versus baseline assessment.^20^ Moreover, radiation oncologists participated in several consensus meetings in which delineation variations in a similar case were discussed, leading to a renewed delineation guideline with more specific anatomical landmarks, which guarantees adequate coverage of the lateral compartments. These radiation oncologists also examined the radiotherapy delineations and doses for all LLNs with a short-axisv≥5.0 mm from the Snapshot 2016 study and demonstrated adequate coverage still being associated with considerable LLR risk and that a boost may also not prevent LLR.^21^ This suggests that any additional reduction of LLR rates may only be achieved with LLND surgery.^5 6^

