### Statistics

Analyses will be conducted in Statistical Package for the Social Sciences (SPSS, Chicago, Illinois). LR and LLR will be compared with a percentage of 13% obtained from the two historic cohorts (Consortium and Snapshot) using a one-sample z-test. Baseline characteristics will be described using numbers and proportions for categorical variables; for continuous data, means with 95% CIs or medians with IQR will be used according to the distribution of the data. Clinical data will be described including the type of neoadjuvant treatment, resection margin, height of the tumour, tumour stage (cT/cN stage) and threatened mesorectal fascia (≤1 mm distance). For functional outcomes, descriptive statistics will be used, while quality of life will be analysed using repeated measure analyses. To compare subgroups within the LaNoReC study, χ^2^ tests and Fisher’s exact tests will be performed for categorical variables. Differences in continuous variables will be analysed using student’s t-tests or Mann-Whitney U tests, according to the distribution of the data. A p value of ≤0.05 will be considered statistically significant.

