### Sample size

The sample size is based on a historical control group with an average 3-year LLR rate of 13% (11% Snapshot and 16% Consortium) in low LARC with LLNs ≥7.0 mm after (C)RT+TME (without LLND), which is the current standard treatment in Europe.^5 6 14^ It is hypothesised that (C)RT+TME+LLND can reduce this rate to 6%, as found by the Consortium study. A one-group χ^2^ test with a 5% two-sided significance level will have 90% power to detect the difference between the null hypothesis proportion of 0.13 and the alternative proportion of 0.06 when the sample size is 190. If correcting for a drop-out rate of 5%, 200 patients are needed. Included patients in need of more extensive surgery (ie, pelvic exenteration or presumed inability to spare the hypogastric nerves on MRI) will be registered and analysed as a separate cohort since these more extensive tumours have higher LLR rates and cannot undergo nerve-sparing LLND.

Annually, approximately 882 patients present with low LARC and are treated with neoadjuvant therapy in the Netherlands.^14^ Considering 122 (14%) of these patients have LLNs ≥7.0 mm, a minimum 2.5-year inclusion period is needed to achieve the estimated sample size (expecting 60% of eligible patients to be enrolled).^14^ As some of the eligible patients will undergo open surgery, it is expected that the inclusion period may require an extension. An interim analysis will be carried out after the inclusion of the first 75 participants. The goal of this interim analysis is to evaluate early indicators of effectiveness concerning oncological outcomes, particularly LLR rate, and to evaluate safety by examining short-term surgical complications (within 90 days) and early functional outcomes (urogenital dysfunction within 3 months). The results will help improve the preoperative information provided to patients. If the interim analysis reveals a high LLR rate that suggests that the hypothesis may not be achievable or significant morbidity within 3 months of surgery, the study team will consider to prompt the study ahead of time.

Additionally, patients with rectal cancer and an LLN of 5.0–6.9 mm SA with at least one malignant feature will be investigated. For this analysis, a sample size calculation is impossible due to limited data. Therefore, all eligible patients in this group will be collected during the study period.

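### The primary 3-year LLR rate is tested as a simple proportion against 13%, with no stated provision for death or loss before 36 months, so the result depends on how those patients are counted

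*Protocol article*

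**What the plan says.** The abstract defines the endpoint at a fixed time: "The primary outcome is LLR rate 3 years postoperatively". The Statistics section fixes the test: both LR and LLR are set against 13% "obtained from the two historic cohorts (Consortium and Snapshot) using a one-sample z-test". The Sample size section treats the rate as a binomial proportion. It plans a one-group chi-square test at a "5% two-sided significance level will have 90% power" for "the null hypothesis proportion of 0.13 and the alternative proportion of 0.06 when the sample size is 190", and then adds: "If correcting for a drop-out rate of 5%, 200 patients are needed".

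The benchmark is also tied to a time point. The Sample size section describes it as an "average 3-year LLR rate of 13% (11% Snapshot and 16% Consortium"), and the Introduction says that the Snapshot cohort "demonstrated a 3-year LLR rate of 11% (4 years 15"%). The Follow-up section plans oncological follow-up of 36 months or longer for each patient.

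The Statistics section names no time-to-event method, although disease-free and overall survival are secondary outcomes. It gives no rule for a patient who dies or is lost before 36 months without LLR. The article does not say whether the 11% and 16% are Kaplan-Meier, cumulative-incidence or crude rates.

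**The concern.** A one-sample test of a proportion needs a yes or no at 36 months for every patient in the denominator. Some patients with locally advanced rectal cancer will die or be lost before then without LLR, and they have to be either counted as LLR-free or left out. The first choice lowers the observed rate. The second raises it, because patients with an early LLR stay in while the others leave the denominator.

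In a single-arm study the whole primary conclusion rests on one estimate set against one external figure. If the two are built by different rules, part of the difference comes from the rules. The direction then follows from an analyst's choice that the article leaves open while it fixes the test itself.

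**Working it through.** **Reproducing the plan's figure.** Inputs from the Sample size section: p0 = 0.13, p1 = 0.06, two-sided 5%, 90% power.

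n = [1.960 × √(0.13 × 0.87) + 1.2816 × √(0.06 × 0.94)]² / (0.13 − 0.06)² = (0.6591 + 0.3044)² / 0.0049 = 189.45, so 190. Then 190 / 0.95 = 200. Both stated numbers are correct for the stated test.

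**Rejection limit.** With n = 190, 15 events give z = (15/190 − 0.13) / √(0.13 × 0.87 / 190) = −2.09, and 16 events give −1.88. Success therefore means at most 15 LLRs. If the true rate is 13% and follow-up is complete, P(X ≤ 15) = 1.9%, against a nominal lower tail of 2.5%.

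**Model for incomplete patients.** My assumptions are constant hazards, independent loss, and a true net (Kaplan-Meier type) 3-year LLR rate of 13%. The 5% loss is the plan's drop-out figure. The article gives no mortality figure, so 15-20% death without LLR by 3 years is assumed.

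- LLR: h = −ln(0.87)/3 = 0.0464
- Death: m = −ln(1 − d)/3 = 0.0542 (d = 0.15) or 0.0744 (d = 0.20)
- Loss: c = −ln(0.95)/3 = 0.0171
- With T = h + m + c, the observed proportion with LLR is (h/T) × (1 − exp(−3T)).

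Example with 5% loss and no deaths: exp(−3T) = 0.87 × 0.95 = 0.8265, so the proportion is (0.0464/0.0635) × 0.1735 = 0.127. The fraction lost before an event is 0.0467, so excluding the lost gives 0.1268 / 0.9533 = 0.133.

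Example with 15% deaths and no loss: exp(−3T) = 0.87 × 0.85 = 0.7395, so the proportion is (0.0464/0.1006) × 0.2605 = 0.120.

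Example with 15% deaths and 5% loss, both excluded: 0.1173 with LLR and 0.7025 alive, followed and LLR-free, so 0.1173 / 0.8198 = 0.143.

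| Deaths (assumed) | Lost | Handling | Observed rate when the net rate is 13% | Chance of false success, n = 190 |
|---|---|---|---|---|
| 0 | 0 | none needed | 13.0% | 1.9% |
| 0 | 5% | lost counted LLR-free | 12.7% | 2.5% |
| 0 | 5% | lost excluded | 13.3% | below 1.9% |
| 15% / 20% | 0 | deaths counted LLR-free | 12.0% / 11.7% | 4.5% / 6.0% |
| 15% / 20% | 5% | both counted LLR-free | 11.7% / 11.4% | 5.7% / 7.5% |
| 15% / 20% | 5% | both excluded | 14.3% / 14.7% | below 1.9% |

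Using n = 200 (limit 16 events) changes the tabulated false-success values by less than 0.1 percentage point.

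**Cost in power if both groups are excluded.** With a true net rate of 6%, 5% loss and 15-20% deaths, about 163-153 of 200 patients remain evaluable. The observed rate is 6.7-6.8%, and power falls to about 71-64%, against the planned 90%.

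**What a competing-risk estimator changes.** With complete follow-up, the crude proportion with deaths as non-events is the cumulative incidence: (h/(h + m)) × (1 − exp(−3(h + m))) = 12.0% and 11.7% for 15% and 20% deaths. An Aalen-Johansen estimator targets the same values. It removes the loss part (11.7% back to 12.0%, 11.4% back to 11.7%) but not the gap to a Kaplan-Meier benchmark.

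**The case against.** The Statistics section names a test, not how the 3-year rate is estimated. A z-test can be run on a Kaplan-Meier or cumulative-incidence estimate with its standard error, and an article may leave that detail to the full protocol or analysis plan. Planned follow-up reaches the endpoint's time horizon, so administrative censoring before 36 months should be small. With the plan's own 5% loss, no deaths and the lost counted as LLR-free, false success is 2.5%, which is the nominal level.

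Much of this stands, and it limits the point. It does not remove it: the z-test, the chi-square sizing on proportions and the absence of any time-to-event method together make a simple proportion the natural reading. Follow-up length deals with administrative censoring, not with death or loss.

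A reader might go further and infer three things that the article does not support.

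- That the comparison is biased towards success. This needs Kaplan-Meier type historical rates, which is nowhere stated. Rates quoted at successive years fit a cumulative incidence equally well. Direction also depends on handling, since exclusion works against the study.
- That the 5% allowance leaves out deaths. Drop-out is not defined, so this cannot be said.
- That a competing-risk estimator alone would cure the death-related shift. It gives the same 12.0-11.7%.

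**Conclusion.** The point holds as a weakness in how the primary analysis is fixed, not as a demonstrated bias. The plan's wording leads to a binomial proportion whose value depends on an unstated choice about incomplete patients.

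From the plan's own 5% loss the effect is small, about 0.3 percentage points either way. With assumed mortality of 15-20% it is larger. Excluding dead and lost patients moves 13% to 14.3-14.7%. Counting deaths as LLR-free moves it to 12.0-11.7%, with false success at 4.5-6.0% instead of 1.9%, but only if the benchmark is a Kaplan-Meier type rate. For a cumulative-incidence benchmark that last component is zero.

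The results rest on constant hazards, independent loss and the assumed mortality. The sample size of 190, raised to 200, is not in error.

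**What to change.** In the Statistics section, define 36-month LLR as a cumulative incidence counted from surgery, with death without LLR as a competing event and censoring at last follow-up. Test it against the benchmark using the standard error of that estimate. Apply the same to LR, with death without LR as the competing event. This removes the loss-related bias and settles how deaths are counted.

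Separately, confirm which estimator produced the 11% and 16%. If they are Kaplan-Meier rates, put both sides on the same estimator: either re-estimate the historical rates from the cohort data, or report a matching Kaplan-Meier estimate for the study as a sensitivity analysis.

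Make both changes before LLR results are seen, and so before the interim look planned after 75 inclusions.

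The cost is revised wording and software that can do competing-risk estimation; the plan names SPSS, so check that it suffices. If re-estimation is chosen, access to the historical patient-level data is also needed, which is the more demanding part. No extra patients and no change to treatment are required.

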### Nerve-sparing LLND procedure by trained surgeons

LLNDs will only be performed by a select team of surgeons after completing adequate human cadaver training, intensive proctoring and assessment of procedural videos. Only surgeons who participated in this training can be nominated with their hospital to act as referral centre or the surgeons can be invited to perform the resection in the (local) referring centre. All ‘study-LLND’ procedure videos will be discussed during monthly meetings for quality control.

Patients with primarily enlarged (≥7.0 mm SA) LLNs are advised to undergo an LLND. Moreover, LLND should be considered in patients with an intermediate (5.0–6.9 mm SA) LLN with at least one malignant feature. LLNDs should be performed according to a minimally-invasive, nerve-sparing technique. If preoperative MRI shows the lateral extension of the tumour into the nerve plexus or an exenteration is required, the patient will still be included to analyse oncological and functional outcomes; however, the patient is not included in the main analyses (see sample size section). If in a shared decision-making process, the patients decide not to undergo an LLND, they remain in the study and are followed for collection of oncological outcomes. In case of a complete clinical response of the tumour and shrinkage of the LLN(s), a patient may enter a watch-and-wait protocol; in these cases, patients should be closely monitored and an LLND may be omitted.

The surgical technique for LLNS has been previously described in detail.^24^ The procedure involves the excision of all lateral lymphatic tissues within the internal iliac and obturator compartment along three anatomical planes: (1) the medial plane defined by the ureter and pelvic plexus (ureterohypogastric fascia), (2) the lateral plane bounded by the psoas and internal obturator muscle and (3) the dorsal plane defined by the internal iliac vessels and the sciatic nerve. It is important to note that the lymphatic tissue along the external iliac arteria is not dissected during this procedure.

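### Minor: the Statistics section fixes Student's t-test for secondary subgroup contrasts without regard to variance, and summarises continuous baseline data by a CI of the mean instead of the SD

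*Protocol article*

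**What the plan says.** All the relevant choices stand in the Statistics section of the protocol article.

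- **Subgroup contrasts.** The sentence on categorical tests opens "To compare subgroups within the LaNoReC study". The next one covers continuous variables: "Differences in continuous variables will be analysed using student’s t-tests or Mann-Whitney U tests, according to the distribution of the data". The threshold follows: "A p value of ≤0.05 will be considered statistically significant". No subgroup is named there and no subgroup size is given.
- **Baseline data.** The rule is "for continuous data, means with 95% CIs or medians with IQR will be used according to the distribution of the data".
- **Main outcomes.** These have other methods. The primary outcome is a proportion (Abstract: "The primary outcome is LLR rate 3 years postoperatively"), and its test is stated as "LR and LLR will be compared with a percentage of 13% obtained from the two historic cohorts (Consortium and Snapshot) using a one-sample z-test". For the rest: "For functional outcomes, descriptive statistics will be used, while quality of life will be analysed using repeated measure analyses".

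Other sections show which subgroups could arise. Patients who decline lateral lymph node dissection (LLND) stay under follow-up (section on the nerve-sparing LLND procedure: "the patients decide not to undergo an LLND, they remain in the study"), and those entering watch-and-wait may omit it. The Sample size section plans 200 patients with enlarged nodes but sets no number for the intermediate-node group.

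**The concern.** Student's t-test pools the two variances. The pooled standard error is right when the variances are equal, and close to right when the groups are of equal size. When sizes and variances both differ, it is wrong in a predictable direction. It is too small if the smaller group is the more variable, which gives too many false positives. It is too large if the larger group is the more variable, which gives too few rejections and missed differences.

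The protocol's only alternative, Mann-Whitney, is triggered by distribution shape and so does not respond to unequal variance. Any subgroups in this study arise from patient choice, tumour response or node size and not from allocation, so the design guarantees neither equal sizes nor equal variances. At stake is whether a secondary p value at or below 0.05 means what it says.

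The baseline rule raises a separate, descriptive problem. A single-arm study judged against historical cohorts needs a baseline table that shows how patients vary. A CI of the mean narrows as n grows and does not describe that variation. The alternative in the same sentence, the median with IQR, does describe spread, so the two halves of the rule answer different questions.

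**Working it through.** **The plan's own figure.** The documents give no figure for any continuous subgroup comparison. The only related figure is the sample size for the primary test (Sample size section: 0.13 versus 0.06, two-sided 5%, 90% power):

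n = [(1.960·√(0.13·0.87) + 1.2816·√(0.06·0.94)) / 0.07]² = [(0.6591 + 0.3044) / 0.07]² = 189.45, so 190; and 190/0.95 = 200.

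It reproduces, and nothing below changes it.

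**Inputs for the t-test check.** The nominal level of 5% is from the Statistics section. Group sizes and SD ratios are assumptions, because the documents give none. Data are normal with equal means.

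**Large-sample formula.** With group sizes n₁, n₂ and SDs s₁, s₂:

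- true variance of the difference: V = s₁²/n₁ + s₂²/n₂
- variance used by Student's test: P = [((n₁−1)s₁² + (n₂−1)s₂²)/(n₁+n₂−2)]·(1/n₁ + 1/n₂)
- actual level: 2·[1 − Φ(1.96·√(P/V))]

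*Sizes 150 and 40, smaller group's SD 1.5 times the larger group's:*

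- V = 1/150 + 2.25/40 = 0.06292
- P = [(149 + 39·2.25)/188]·(1/150 + 1/40) = 1.2593·0.03167 = 0.03988
- √(P/V) = 0.796; 1.96·0.796 = 1.560; level = 11.9%

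*Same sizes, larger group's SD 1.5 times the smaller group's (ratio 2/3):*

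- V = 1/150 + 0.4444/40 = 0.01778
- P = [(149 + 39·0.4444)/188]·0.03167 = 0.8848·0.03167 = 0.02802
- √(P/V) = 1.255; 1.96·1.255 = 2.460; level = 1.4%

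**Simulation** (40,000 runs per cell, SD ratio 1.5, rejection rate at p ≤ 0.05):

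| Sizes | Student, smaller group more variable | Student, larger group more variable | Welch, same two cases |
|---|---|---|---|
| 95/95 | 5.0% | 5.0% | 5.0%, 5.0% |
| 130/60 | 8.8% | 2.4% | 4.9%, 5.1% |
| 150/40 | 11.8% | 1.4% | 5.0%, 5.0% |
| 170/20 | 15.0% | 0.7% | 4.9%, 5.0% |

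The range over other ratios at 150/40 is 8.3% or 2.4% at ratio 1.25, and 17.3% or 0.5% at ratio 2. Over all assumed splits and ratios from 1 to 2, Welch's test stays between 4.9% and 5.2%.

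**When nothing goes wrong.** With equal SDs, Student's test holds about 5% even at 170/20. With equal sizes, it holds about 5% even at SD ratio 2. Both inequalities are needed.

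**Mann-Whitney** (4,000 runs per cell, 150/40, ratio 1.5): 8.6% when the smaller group is more variable and 2.6% in reverse. The stated alternative does not remove the problem.

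**Baseline summary.** The CI half-width for a mean at n = 200 is 1.96/√200 = 0.139 SD. The central 95% of normally distributed patients spans ±1.96 SD. The ratio is √200 = 14.1, so the CI is about one-fourteenth as wide as the patient range.

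**The case against.** The strongest reply is that the t-test problem depends on conditions that the documents do not establish. No subgroup is named, no size is given and no SD is reported. A non-randomised design brings confounding; it does not by itself make variances unequal. Unequal size alone does no harm, as shown above. All of this stands, and it is why the error rates are illustrations under assumed inputs.

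A reader might infer that quality-of-life or functional results would be tested this way, or that the extensive-surgery cohort would be compared with the main cohort. The documents do not support either inference. Quality of life has repeated-measures analyses, functional outcomes are only described, and the Sample size section analyses the extensive-surgery patients as a separate cohort with no planned test against the others. A reader might also infer that the sample size or the LLR conclusion is at risk; neither uses a t-test.

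It can also be said that pooled versus unequal-variance is a detail for an analysis plan that is not shown. This has some force, since the article never writes out the variance assumption. But it does name Student's test and the rule for leaving it, so this is a stated choice and not a gap. Unequal variance is not far-fetched either. The eligibility range confines intermediate nodes to 5.0–6.9 mm, so their short-axis SD cannot exceed half that range, (6.9 − 5.0)/2 = 0.95 mm, while enlarged nodes have no upper limit. Testing baseline node size between groups defined by it would be pointless, but related measures could carry the same imbalance.

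On the baseline table, the SD can be recovered as half-width·√n/1.96 when n is reported, skewed variables get medians with IQR, and several of the listed descriptors are categorical. That makes the flaw one of presentation, but it does not make the CI the right summary.

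**Conclusion.** The point holds as a minor one. The Statistics section commits to a test whose level is not assured if subgroup sizes and variances both differ, and its only switch ignores variance. Under assumed 150/40 groups with an SD ratio of 1.5, the actual level is about 12% or 1.4%, depending on which group is more variable; the documents neither confirm nor exclude such conditions. The baseline point needs no assumption about subgroups: the mean with a 95% CI does not describe the spread of patients. The consequences are confined to secondary subgroup contrasts of continuous variables and to the baseline table.

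**What to change.** Two wording changes in the Statistics section:

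1. Replace *student's t-tests* with *Welch's unequal-variance t-tests*, and report the mean difference with its 95% CI.
2. For baseline characteristics, replace *means with 95% CIs* with *means with SDs*, and keep the median with IQR for skewed variables.

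The cost is a negligible loss of power when variances happen to be equal. SPSS, the package the protocol names, already prints the unequal-variance result and the SD. Sample size, data collection and the primary analysis stay as they are.
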